|                                                  |                                                                                                                                                                                                                                                                                                                                                                                                                                                                                                                                                                                                                                                                                                                                                                                                |
|--------------------------------------------------|------------------------------------------------------------------------------------------------------------------------------------------------------------------------------------------------------------------------------------------------------------------------------------------------------------------------------------------------------------------------------------------------------------------------------------------------------------------------------------------------------------------------------------------------------------------------------------------------------------------------------------------------------------------------------------------------------------------------------------------------------------------------------------------------|
| 
Expected total number of patients:
 | 
d) Patient is immunocompromised;
e) Patient is on a course of anti-inflammatories or antibiotics;
f) Patient has diabetes mellitus (DM).
 
60 patients, 30 in the treatment group and 30 in the control group, stratified as follows:
 
Arm 1) Considered the control group, this arm will receive conventional treatment from the date of admission to the hospital and will also receive the protocol with the laser turned off, therefore without any effect.
 
Arm 2) This arm will receive the laser treatment within 30 minutes after the infusion of antivenom serum at a dose of 4j/cm^2.
                                                                                                                                                      |

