|                                     | 
of creatine phosphokinase activity, pain intensity, circumference measurement ratio, extent of edema, difference between the bite-site temperature and that of the contralateral limb, and disability assessments, were compared using the t-test for independent samples, at 48 hours after admission. A Kaplan-Meier survival analysis with a log-rank test was performed to detect differences in the time elapsed from admission to the day of reduction by 50% in creatine phosphokinase activity, pain intensity, circumference measurement ratio, extent of edema and difference between the bite-site temperature and that of the contralateral limb between the intervention and comparator groups, at two points - on 24 and on 48 hours after admission. The comparison of the frequency of use of analgesics, secondary infections and necrosis in a follow-up of 48 hours, between the intervention and comparator groups, was made using the Chi-square or Fisher's exact test; odds ratios with 95% confidence intervals were obtained. The Kruskal-Wallis rank sum test was used to compare the disability scores between groups, for each domain score and for the summary score. Statistical analyses were performed in the R software in the IDE Rstudio environment (version 4.1.2), and the significance level of the tests was 0.05.
 |

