## 7. PATIENT SELECTION

### 7.1. Number of patients planned

The research patients will be allocated into 2 main arms:

- **Arm 1:** Thirty patients bitten by *Bothrops* snakes who received regular FMT treatment.

[figure not shown][figure not shown]

- 
- **Arm 2:** These patients will receive the laser within 30 minutes after administration of the antivenom serum at a dose of 4 J/cm^2.

**First phase T1** - first laser application and first clinical evaluation will take place as follows:

- **Arm 1**, considered control, will receive the conventional treatment from the date of admission to the hospital and will also receive the laser, but turned off, therefore without any effect.
- **Arm 2**, will receive the laser within 30 minutes after administration of the antivenom serum at a dose of 4 J/cm^2.

**Second phase T2** - The groups will receive the same laser therapy regimen to which they were randomized within 24 hours.

**Third phase T3** - 48 hours after the first application. On the 3rd day, the patient is discharged from the hospital if they are well.

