## 9.2 Secondary

### Prevention of myonecrosis

Efficacy should be evaluated according to the results of creatine kinase (CK) in the follow-up period (see Appendix A).

- The increase in CK indicates myonecrosis, which should be investigated from the first moment with the patient and after 24 h, 48 h and 72 h. When the patient returns on the 7th day, CK testing will also be performed and evaluated in the two arms of the clinical trial.

Other secondary parameters include:

- Proportion of any adverse events, such as itching, skin redness, changes in skin pigmentation, bruising, scarring, peeling, skin depression, and textural and thickness changes.

[figure not shown][figure not shown]

---

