### 13.2 Statistical and analytical plans

Feasibility outcomes were analyzed using descriptive statistics as proportions. Trial outcomes were reported as means and standard deviations. We report the outcomes using means and standard deviations, and we conducted inferential analysis on our data in order to report the differences between the two groups. Mean values of creatine phosphokinase activity, pain intensity, circumference measurement ratio, extent of edema, difference between the bite-site temperature and that of the contralateral limb, and disability assessments, were compared using the t-test for independent samples, at 48 hours after admission. A Kaplan-Meier survival analysis with a log-rank test was performed to detect differences in the time elapsed from admission to the day of reduction by 50% in creatine phosphokinase activity, pain intensity, circumference measurement ratio, extent of edema and difference between the bite-site temperature and that of the contralateral limb between the intervention and comparator groups, at two points - on 24 and on 48 hours after admission. The comparison of the frequency of use of analgesics, secondary infections and necrosis in a follow-up of 48 hours, between the intervention and comparator groups, was made using the Chi-square or Fisher's exact test; odds ratios with 95% confidence intervals were obtained. The Kruskal-Wallis rank sum test was used to compare the disability scores between groups, for each domain score and for the summary score. Statistical analyses were performed in the R software in the IDE Rstudio environment (version 4.1.2), and the significance level of the tests was 0.05.

[figure not shown][figure not shown]

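### Section 13.2 gives disability two between-arm analyses at 0.05, a t-test at 48 hours and an undated Kruskal-Wallis test of every domain and the summary, names neither as decisive, and no objective or outcome shown lists disability

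*Protocol*

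**What the plan says.** The statistical paragraph in section 13.2, which also stands in the synopsis under Statistical considerations, treats disability twice.

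- In the list of means compared between arms, the last item reads "and disability assessments, were compared using the t-test for independent samples, at 48 hours after admission".
- Later in the paragraph: "The Kruskal-Wallis rank sum test was used to compare the disability scores between groups, for each domain score and for the summary score". No time is attached to this sentence.
- For all of this, "the significance level of the tests was 0.05". No rule says which analysis of disability decides.

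The instrument, the number of domains and the direction of scoring are not given. Disability is not named in the objectives (5.1, 5.2), in the primary outcome of reduced inflammation with its tolerability assessments (9.1), or in the secondary outcomes, which are myonecrosis judged by CK and adverse events (9.2). The planned size is "60 patients, 30 in the treatment group and 30 in the control group".

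**The concern.** An outcome with two unranked tests leaves the choice of p-value open until the data are seen. The t-test compares means and the Kruskal-Wallis test compares ranks, so on skewed scores they can lead to different conclusions. The second analysis is also a family of tests, one per domain plus the summary, each at 0.05.

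Since section 9 does not list disability, nothing fixes in advance which of these results would count. A significant domain, or whichever test gave the smaller p-value, could be presented as a finding of the trial.

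Of the items in the t-test list, only disability has a second test of its level between arms. The Kaplan-Meier analyses of CK, pain, circumference, edema and temperature address a different quantity, the time to a 50% reduction.

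**Working it through.** **No figure to reproduce.** The protocol states no effect size, SD or power for disability. The check is a comparison of passages followed by a simulation on stated assumptions.

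**Step 1: passages side by side.**

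| Item | First analysis | Second analysis |
|---|---|---|
| Wording for the variable | disability assessments | disability scores |
| Test | independent-samples t-test | Kruskal-Wallis |
| Applied to | mean values | each domain and the summary |
| Time | 48 hours after admission | none stated |
| Level | 0.05 | 0.05 |
| Decisive? | not stated | not stated |

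**Step 2: one score, two tests.** Inputs from the protocol: 30 per arm, level 0.05 (taken as two-sided). Assumed: the score distribution. Both tests were run on the same data, 20,000 trials per row. The Monte Carlo standard error is √(p(1−p)/20,000), about 0.002 at p = 0.06 and 0.003 at p = 0.17.

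No true effect:

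| Assumed scores | t-test | Kruskal-Wallis | Either significant | Tests disagree |
|---|---|---|---|---|
| Normal | 0.048 | 0.048 | 0.057 | 1.9% |
| 5-level ordinal | 0.050 | 0.051 | 0.062 | 2.4% |
| Bounded 0–100, skewed | 0.051 | 0.052 | 0.068 | 3.2% |
| Lognormal | 0.048 | 0.051 | 0.070 | 4.1% |

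With a true effect:

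| Assumed scores and effect | Power, t-test | Power, Kruskal-Wallis | Tests disagree |
|---|---|---|---|
| Normal, 0.75 SD | 81% | 79% | 5.1% |
| Lognormal, shift 0.55 on a log SD of 0.8 | 63% | 73% | 17.7% |
| Bounded, skewed: beta(0.6, 1.8) against beta(0.6, 3.6) | 55% | 42% | 16.5% |

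Either test can be the more powerful one, depending on a distribution the protocol does not describe.

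**Step 3: all domains plus the summary.** With d domains there are d + 1 rank tests. Under independence the family-wise error is 1 − 0.95^(d+1):

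- d = 3: 1 − 0.95^4 = 0.19
- d = 8: 1 − 0.95^9 = 0.37

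Domains of one instrument are correlated, so these are upper bounds. Simulated with normal domain scores, the summary as their sum, 30 per arm and 3,000 trials per setting (standard error about 0.007 at p = 0.2), the chance of at least one significant Kruskal-Wallis result is:

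| Correlation | 3 domains | 6 domains | 8 domains |
|---|---|---|---|
| 0.3 | 0.15 | 0.25 | 0.31 |
| 0.5 | 0.12 | 0.22 | 0.25 |
| 0.7 | 0.11 | 0.18 | 0.20 |

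The range is therefore about 0.11 to 0.31. If either test could be reported on each score, it would be about 0.14 to 0.36.

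**Step 4: after the fix.** One named test on one summary score at one time keeps the error at 0.048 to 0.052 in the simulations of step 2.

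**The case against.** **The same scores are not confirmed.** The two sentences use different nouns, no instrument is named, and the 48-hour time belongs to the t-test sentence alone. This stands as a qualification. The natural reading is still one set of scores, and if two sets were meant, the protocol would need to say so.

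**The type I error from choosing a test is small.** This stands: it is 0.057 to 0.070 for one score. The weight lies in disagreement under skewed scores and in the domain tests.

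**Multiplicity rules are often left to an SAP.** True, and no SAP is at hand. But the protocol itself fixes two unranked analyses of one outcome, and an SAP would have to overrule it.

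**Other variables are also tested without being listed.** Analgesic use and secondary infection are compared in 13.2 but are not outcomes in section 9. That is correct, but they have one comparison each, with chi-square and Fisher's exact test offered as alternatives.

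Some stronger readings are tempting and are not supported:

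- *That 48 hours is the wrong time for disability.* A reader might infer this because 48 hours is day 3 of the hospital stay, when "the patient is discharged from the hospital if they are well", and because the rationale in 4.1 mentions disabling lesions and lost work. But the instrument is unknown. A limb-function scale could be scored at the bedside, and the primary objective concerns acute local manifestations.
- *That disability should move to day 7.* Section 9.2 says "When the patient returns on the 7 th day, CK testing will also be performed", but describes that return for CK only. Section 12.1.1 covers D1 to D3, and sections 6.2 and 11 describe return after the hospital period only for complaints or worsening.
- *That no visit or form collects disability.* The flowchart in 12.1 is not shown and the form items run from 2 straight to 8, so such a form may exist. Only the absence from the objectives and outcomes can be shown.
- *That the false-positive risk is 26% to 37%.* This comes from assuming 4 to 7 domains and counting one t-test as a further independent test (1 − 0.95^6 and 1 − 0.95^9). A t-test and a rank test of the same score are strongly dependent, as are the domains.

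**Conclusion.** The point holds in limited form. The protocol specifies two unranked between-arm analyses for disability, one of them undated and spread over an unstated number of domains, for a variable missing from the objectives and outcomes shown.

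The main effect is on what may be reported: about one trial in six gives conflicting conclusions if there is an effect and scores are skewed (about 5% if they are normal), and at least one domain or summary test is falsely significant in about 11% to 31% of trials.

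These sizes rest on assumed distributions and effects, 3 to 8 domains, correlations of 0.3 to 0.7, and both tests using the same scores. The primary outcome is not affected.

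**What to change.** 1. In 13.2 and in the synopsis, delete *disability assessments* from the list of means compared by t-test.
2. Keep one rank-test comparison of the summary score, at one stated time. The only time the protocol attaches to disability is 48 hours.
3. Report the domain scores descriptively, without p-values.
4. List the summary score once in 9.2 as a secondary outcome, with the instrument named. If this is not wanted, drop disability from the comparative analyses.

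The cost is wording in three places, with no added visit. Two things are given up: p-values for single domains, and some power if the scores have a shape that favors the t-test, as in the bounded-skewed case (55% against 42%). For the lognormal case the rank test gains (73% against 63%).

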## **14. ETHICAL AND REGULATORY STANDARDS**

### **14.1 Ethical principles**

This clinical study will be carried out following the Resolutions 466/2012 and 580/2018, and the relevant Brazilian regulations.

The study will be forwarded through the Plataforma Brasil to the Research Ethics Committee of the Amazonas State University and will be registered in the Brazilian Registry of Clinical Trials (ReBEC). Patients must sign the ICF to participate in the research.

This clinical trial was registered on a website (Registro Brasileiro de Ensaios Clínicos - ID RBR-2rcm2g) before the inclusion of the first patient. It presents basic information about the trial that is sufficient for interested patients (and healthcare professionals) to know how to participate in the trial.

This study was registered in the Brazilian Registry of Clinical Trials (ReBec): RBR-4qw4vf and UTN Number: U1111-1244-4898.

### **14.2 Laws and regulations**

This clinical trial will be carried out in compliance with all international laws and regulations and with the laws and regulations of Brazil, where the clinical trial is carried out.

### **14.3 Informed consent and assent**

The investigator (in accordance with applicable regulatory requirements), or someone designated by the investigator, but under the investigator's

[figure not shown][figure not shown]

responsibility, shall inform the patient or the patient's parents or guardians of all the pertinent aspects of the clinical trial, including from written information outlining the approval/favorable opinion from the local REC. All participants should receive as much information about the study as possible, in language and terms they can understand.

Before a patient participates in the clinical trial, the written informed consent form and any other applicable local documents in accordance with local laws and regulations must be signed, with the name and date filled in by the patient or their legal representative, and by the person who talked about the informed consent form. The patient should keep a copy of the signed and dated informed consent form.

- Participants who can read the informed consent form/assent form must do so before entering their name and date and signing the form.
- In the case of participants who know how to write, but not how to read, the informed consent form/assent form will be read aloud before they enter their name and date.
- In the case of participants who can understand, but who cannot read and write, the informed consent form will be read aloud in the presence of an impartial witness, who will sign and date the informed consent form to confirm that consent has been given.

The informed consent form used by the investigator to obtain the patient's informed consent must be evaluated and approved by the sponsor prior to submission to the relevant Ethics Committee for approval/favorable opinion.

[figure not shown][figure not shown]

---

## 15. CONFIDENTIALITY

All information disclosed or provided by patients or produced during the clinical trial, including, but not limited to, the clinical trial protocol, the CRFs, the investigator's brochure and the results obtained during the trial are confidential.

The investigator and anyone under the investigator's authority agrees to keep this information confidential and not to disclose this information to any third party.

However, the presentation of this clinical trial protocol and other necessary documents to the ethics committee is expressly permitted, bearing in mind that members of ethics committees have the same duty of secrecy.

The investigator and sub-investigators must use the information exclusively for the purposes of the clinical study, avoiding any personal use or in favor of a third party.

## 16. CLINICAL STUDY RESULTS

The researcher will be responsible for preparing a clinical study report. Regardless of the outcome of the study, the researcher undertakes to publish the results.

## 17. PUBLICATIONS AND COMMUNICATIONS

The researcher recognizes the right to use data from the clinical study in courses, conferences and scientific publications. However, to ensure the accuracy and scientific value of the information, while preserving the investigator's independence and responsibility, and the confidentiality of the information, only

[figure not shown][figure not shown]

verified and validated data will be used. For this, it is essential that the parties agree before any publication or communication is carried out by the investigator.

Study results must be submitted for review by the steering committee prior to publication. All study investigators and committee members fully authorize the steering committee to present or publish priority results. However, in the absence of publication within 12 months of completion of the clinical trial at all centers, the steering committee, if applicable, may consider the investigator's request for independent publication. If no publication occurs within 12 months of the end of the clinical trial, the investigator shall have the right to independently publish the results of that clinical trial, subject to the review procedure set forth herein. The steering committee may stipulate specific rules for publication.

No further publication is permitted prior to primary publication. Any presentations or subsequent publications made by study participants must be approved by the researcher in charge, making reference to the study and the primary publication.

## 19. ATTACHMENTS

## ATTACHMENT A

**1. Patient Data**

1.1 Phone contact: ( ) \_\_\_\_\_ ( ) \_\_\_\_\_  
1.2 Address: \_\_\_\_\_ n° \_\_\_\_\_ District: \_\_\_\_\_  
1.3 City: \_\_\_\_\_  
1.4 Gender: • 1-Male 2-Female  
1.5 Birth date \_\_\_\_/\_\_\_\_/\_\_\_\_ 1.6 Age: ••

**2. Snakebite Data**

2.1 Origin: • 1-Manaus 2-Municipality Where? \_\_\_\_\_  
2.2 Date of the accident: \_\_\_\_/\_\_\_\_/\_\_\_\_  
2.3 Estimate time of the accident: \_\_\_\_:\_\_\_\_  
2.4 Date of admission to FMT-HVD: \_\_\_\_/\_\_\_\_/\_\_\_\_ 2.5 Time of Admission: \_\_\_\_:\_\_\_\_  
2.6 Date of discharge from FMT-HVD: \_\_\_\_/\_\_\_\_/\_\_\_\_  
2.7 Reason: • 1-Discharge 2-Death 3-Transference  
2.8 Zone of Occurrence: • 1-Rural 2-Urban 3-Peri-urban 9-Ignored  
2.9 Place of bite: • 1-Head 2-Arm 3-Leg 4-Torso 5-Neck 6-Hand  
7-Thigh 8-Forearm 9-Foot 10-Other (Specify): \_\_\_\_\_  
2.10 Affected side of the body: • 1-Right 2-Left 3-Center  
2.11 Stood or walked after the accident: • 1-No 2-Yes For how long? \_\_\_\_ min.  
2.12 Accident related to work: • 1-No 2-Yes  
2.13 Prior accident: • 1-No 2-Yes How many? \_\_\_\_  
Date of the last accident: \_\_\_\_/\_\_\_\_/\_\_\_\_ (mm/yyyy)

Signature and Stamp: \_\_\_\_\_

[figure not shown][figure not shown]

CEPCLAM

VERSION 2.0 / DATE 06/06/2018

| Laser Therapy           |    |    |    |    |
|-------------------------|----|----|----|----|
|                         | D1 | D2 | D3 | D7 |
| Energy (J)              |    |    |    |    |
| Dose (cm  ) |    |    |    |    |
| Time                    |    |    |    |    |
| Power                   |    |    |    |    |
| Anatomic Points         |    |    |    |    |
| Place                   |    |    |    |    |

| Thermography            |    |    |    |    |
|-------------------------|----|----|----|----|
|                         | D1 | D2 | D3 | D7 |
| Ambient temperature     |    |    |    |    |
| Body temperature        |    |    |    |    |
| Software                |    |    |    |    |
| Temperature scale/range |    |    |    |    |
| Emissivity standard     |    |    |    |    |
| Anatomic Area           |    |    |    |    |
| Color/Temperature       |    |    |    |    |

ATTACHMENT B

**8. Patient's Clinical Data - Day 1**

**8.1 Date of assessment:** | | | | | | | | **8.2 Time:** \_\_\_\_:\_\_\_\_

**8.3 Blood pressure** | | | | | / | | | | | mm Hg **8.4 Pulse** | | | | | min

**8.5 Temperature** | | | | | °C **8.6 Respiratory rate** | | | | | rpm

